### Interventions

Participants in the intervention group will be helped to download KOKU-Nut onto their iPad or tablet during the baseline visit. The researcher (CF) will demonstrate the features and assist with any technical queries. In cases where participants do not have the necessary devices or data to join the intervention, a tablet with KOKU-Nut installed will be provided for the duration of the intervention. Participants will be asked to engage with KOKU-Nut at least 3 times a week throughout the 12-week period. This will involve carrying out strength and balance exercises and engaging with the gamification features relating to bone health and healthy eating. A crib sheet and contact details for the research team will be available if participants require additional support to help with technical issues.

Participants assigned to the control group will continue with usual care and receive a leaflet developed by Age UK about the importance of a healthy lifestyle including information on the importance of staying active and nutrition [19]. This will allow the comparison of a more traditional way to provide lifestyle advice compared to the digital health tool.

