### Outcomes

Primary outcomes will be related to feasibility and will assess engagement with the intervention, recruitment and retention rates, and acceptability of the intervention and study design. These findings are important to inform the development of a large-scale RCT in community-dwelling older adults to compare the effectiveness of KOKU-Nut to an information booklet about healthy living. Recruitment rates will be assessed as cumulative recruitment against the target rate each month. Retention rates will be calculated as the number of participants who completed the study divided by the number of participants randomized. Engagement with the intervention will be based on self-reported use of KOKU-Nut at the end of the 12 weeks (every day, 3-4 times a week, 1-2 times a week, and once or twice a month). A questionnaire previously developed and used by the research team for the KOKU app will assess the acceptability of KOKU-Nut [13]. Intervention acceptability will also be assessed using the 11-item, 7-point, modified Treatment Evaluation Inventory [20]. Higher scores indicate higher acceptability, with a score of 44 indicating moderate acceptability. Interviews will explore the acceptability of the intervention and the perceived impact of taking part in the study. Interviews will also consider the participant’s experience of the recruitment process, the assessment tools used, and their experience and motivation for participating in the study (positive and negative).

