Recruitment for the qualitative interviews will be done purposefully, to recruit a demographically representative group of participants. To do this, the sample frame will be divided into a number of smaller groups, namely the treatment group, age, gender, and prior ownership of a tablet or iPad. Individuals will then be drawn at random from each of these groups. We also plan to contact any dropouts to understand their rationale for dropping out to optimize the retention of participants if continuing to a full RCT. Researchers will use the concept of information power [23] to determine the number of interviews, but we anticipate sufficient data will be obtained from interviewing 20% of participants recruited for the study. Figure 2 represents the overall flowchart of participants through the study.

Participants who meet the screening criteria and are interested in taking part will provide informed written consent (Multimedia Appendix 1) before being formally enrolled in the study. During the screening phone call, the researcher (CF) will arrange a date and time suitable for the participant to conduct the initial baseline assessment. Prior to completing baseline measures, participants will be randomized in a 1:1 ratio to receive the intervention (KOKU-Nut) or to the control group and receive usual care.

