### Allocation

Randomization will be undertaken by a separate member of the research team using the Sealed Envelope randomization service [24], and participants will be stratified by age group (65-75 years and 76 years and older), gender, and prior experience of using a tablet or iPad. Given the nature of the intervention, participants and researchers will be unblinded.

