### Data Collection Methods

#### Overview

All participants will receive in the post a baseline case report file to be completed before the baseline assessment to collect sociodemographic information including age, gender, ethnicity, marital status, occupation, use of digital technology, shopping, and cooking habits. Participants will also be asked to complete a 3-day food diary using Intake24 prior to the baseline visit [25]. This web-based dietary assessment tool is compliant with the general data protection regulations (2018), and participants will be sent a unique number that will enable the researcher to identify the digital dietary records. Data collected will be used to assess the consumption of different food groups to identify adherence to the Eatwell guide [14]. During the home visit, the researcher (CF) will collect baseline measurements to assess anthropometry, dietary intake, physical function, quality of life, mood, and frailty. All measurements are responsive to change, appropriate for use in this population, and easily assessed in a community setting.

At the end of the 12-week intervention period, all baseline measures will be repeated, and participants will complete a follow-up case report file to collect feasibility outcome data. The researcher will conduct one-to-one semistructured interviews with a selected group of participants from both the intervention and the control group. Interviews will be conducted in person or over the phone depending on the preference of the participant. Interviews will last approximately 60 minutes, will be audio-recorded, and then transcribed verbatim by the research team. Additional consent will be collected prior to conducting the interview. A topic guide developed for the study will be used flexibly to guide the interviews.

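### Randomisation comes before baseline in an unblinded trial, and no written step withholds the allocation, so baseline measures can be taken with the arm known

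*Protocol article*

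**What the plan says.** The Recruitment section fixes the order: "Prior to completing baseline measures, participants will be randomized in a 1:1 ratio to receive the intervention (KOKU-Nut) or to the control group". The Allocation section adds "Given the nature of the intervention, participants and researchers will be unblinded", with no exception for baseline assessment. It also says "Randomization will be undertaken by a separate member of the research team using the Sealed Envelope randomization service".

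The Overview under Data Collection Methods describes how baseline is gathered. Before the visit, "All participants will receive in the post a baseline case report file to be completed before the baseline assessment" and "Participants will also be asked to complete a 3-day food diary using Intake24 prior to the baseline visit". At the home visit the researcher "will collect baseline measurements to assess anthropometry, dietary intake, physical function, quality of life, mood, and frailty". The Interventions section places an arm-specific activity at that visit: "Participants in the intervention group will be helped to download KOKU-Nut onto their iPad or tablet during the baseline visit".

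Under Statistical Analysis, pre-post changes in health measures are explored against group assignment, and Cohen d is calculated so that a powered trial can be sized. The Outcomes section says the same of the changes in means and SDs.

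**The concern.** A baseline is a fair reference point when it cannot depend on the arm. Here it can. Someone who knows that a healthy-eating app is coming may eat or report differently in the baseline food diary. Someone who knows that a leaflet is coming may put different effort into a grip or chair-rise test. The same researcher role rates frailty, times the sit-to-stand and demonstrates the app.

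Two things are at stake. The first is the between-group difference in change, and through it the effect size passed to the next trial. The second is completeness: a person lost after randomisation but before the home visit has no home-visit baseline and cannot contribute a change in those measures. Using a separate team member and an external service protects the allocation sequence. It does not protect measurements taken after the result is known.

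**Working it through.** The plan has no figure of its own to reproduce on this point. The check sets the sections side by side and then illustrates the size.

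**Order of events.** Recruitment puts randomisation before baseline is complete. Allocation says that nobody is blinded. Interventions has the app installed at the baseline visit, so the arm is known at some point during that visit at the latest. No section says that measurement precedes disclosure or that a blinded assessor takes the baseline. The schedule and flowchart figures are not shown and could not be checked.

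**Which measures are exposed.**
- Self-reported: Intake24 diary, EQ-5D, 4-item depression scale.
- Researcher-rated: clinical frailty scale.
- Effort-dependent: grip strength, 5-times sit-to-stand.
- Little exposed: height and weight.

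**Size of the bias.** The documents give neither a shift nor a baseline to follow-up correlation, so both are assumed. Let knowledge of the arm move one arm's mean baseline by δ (in SD units, equal SDs at both times), with no effect on follow-up. Let ρ be the correlation between baseline and follow-up.
- Difference in change = (follow-up difference) − (baseline difference), so its bias is δ in absolute size.
- Baseline-adjusted difference = (follow-up difference) − ρ × (baseline difference), so its bias is ρδ.

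| δ (SD) | Bias in change | Adjusted, ρ = 0.5 | Adjusted, ρ = 0.7 |
|---|---|---|---|
| 0.1 | 0.1 | 0.05 | 0.07 |
| 0.2 | 0.2 | 0.10 | 0.14 |
| 0.3 | 0.3 | 0.15 | 0.21 |

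If Cohen d is scaled by the SD of change, the change bias is δ/√(2(1−ρ)). At ρ = 0.5 this is again δ. At ρ = 0.7 it is 0.13, 0.26 and 0.39.

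**Effect on the next trial's size.** Assume two-sided 5% and 80% power, neither of which the article states. Then n per arm = 2(1.96 + 0.8416)²/d² = 15.698/d².
- d = 0.3: 15.698/0.09 = 174.4, so 175 per arm.
- d = 0.4 (bias +0.1): 15.698/0.16 = 98.1, so 99 per arm.
- d = 0.2 (bias −0.1): 15.698/0.04 = 392.4, so 393 per arm.

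The sign of any bias cannot be predicted from the documents.

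**Feasibility of the reverse order.** The stratifiers are age group, gender and prior tablet experience. All three can be asked at the telephone screening that Recruitment already describes. Consent already precedes enrolment, and the app is already installed at the baseline visit.

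**The case against.** Much of the case on the other side stands.

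- **Disclosure time is not stated.** Recruitment dates the randomisation, not the moment when the participant or visiting researcher is told. If the separate team member in fact withheld the result until after measurement, most of the bias would disappear. This limits the point to a risk. It does not remove it, because no such step is written.
- **The affected analysis is exploratory.** The primary outcomes are engagement, recruitment, retention and acceptability, and the Sample Size section disclaims any aim of detecting differences. With 18 per arm, the standard error of a standardised difference is about √(2/18) = 0.33 (95% interval about ±0.65). With 20% dropout (14.4 per arm) it is about √(2/14.4) = 0.37. Sampling error is larger than any shift assumed above. However, sampling error shows in an interval, whereas a systematic shift does not.
- **The fix is partial.** Follow-up assessment stays unblinded whatever is done at baseline.

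Two stronger readings are tempting, and the documents do not support them.

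A reader might infer that reversing the order would protect retention from people who leave on learning that they are in the leaflet arm. It would not. The Outcomes section says "Retention rates will be calculated as the number of participants who completed the study divided by the number of participants randomized", so such a person counts as 1/36 = 2.8 percentage points lost whether told before or after baseline. The plan to contact dropouts also treats their reasons as information worth having.

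A reader might also infer that anyone lost before the visit has no baseline at all. The posted file and the diary are due before the visit, so such a person may have returned either. What is missing for certain is the set of home-visit measures.

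**Conclusion.** The point holds as a risk that should be fixed, not as a demonstrated bias or a flaw that undermines the trial. The stated order, the lack of blinding and the absence of any withholding step together allow the exposed baselines to be collected with the arm known. The consequence falls on the exploratory group differences in change and on the Cohen d for the next trial.

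The range of 0.1 to 0.3 SD for a change analysis, or 0.05 to 0.21 SD for an adjusted one, rests on an assumed shift in one arm, correlations of 0.5 to 0.7, and a shift that does not persist to follow-up. If it persisted in full, it would cancel from the change. Those values are illustrations, and the documents support no particular one. The conclusion would weaken if the figures not shown, or the full protocol, place disclosure after measurement.

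**What to change.** Reverse the order in the Recruitment section:
1. Take the three stratifiers at telephone screening.
2. Obtain consent, then have the posted file and food diary completed.
3. Take the home-visit measurements.
4. Only then have the separate team member randomise, or release the result, at the end of the same visit and just before the app is installed or the leaflet handed over.

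For anyone already randomised under the current order, report when the allocation was disclosed relative to each baseline measure, and the number lost before baseline in each arm.

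No extra visit is needed. The costs are a protocol change through the ethics amendment route named under Ethical Considerations, a team member reachable during every home visit, and a researcher equipped for either arm. The Abstract says that data collection began in March 2024, while the Results section still describes the start as anticipated. If enrolment has begun, the sample will be split between two procedures, and the report should say how many participants followed each.

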**Figure 2 figure2:**
[figure not shown]
Flowchart of participants from screening to follow-up.

### Allocation

Randomization will be undertaken by a separate member of the research team using the Sealed Envelope randomization service [24], and participants will be stratified by age group (65-75 years and 76 years and older), gender, and prior experience of using a tablet or iPad. Given the nature of the intervention, participants and researchers will be unblinded.

### Data Collection Methods

#### Overview

All participants will receive in the post a baseline case report file to be completed before the baseline assessment to collect sociodemographic information including age, gender, ethnicity, marital status, occupation, use of digital technology, shopping, and cooking habits. Participants will also be asked to complete a 3-day food diary using Intake24 prior to the baseline visit [25]. This web-based dietary assessment tool is compliant with the general data protection regulations (2018), and participants will be sent a unique number that will enable the researcher to identify the digital dietary records. Data collected will be used to assess the consumption of different food groups to identify adherence to the Eatwell guide [14]. During the home visit, the researcher (CF) will collect baseline measurements to assess anthropometry, dietary intake, physical function, quality of life, mood, and frailty. All measurements are responsive to change, appropriate for use in this population, and easily assessed in a community setting.

At the end of the 12-week intervention period, all baseline measures will be repeated, and participants will complete a follow-up case report file to collect feasibility outcome data. The researcher will conduct one-to-one semistructured interviews with a selected group of participants from both the intervention and the control group. Interviews will be conducted in person or over the phone depending on the preference of the participant. Interviews will last approximately 60 minutes, will be audio-recorded, and then transcribed verbatim by the research team. Additional consent will be collected prior to conducting the interview. A topic guide developed for the study will be used flexibly to guide the interviews.

#### Anthropometry

A member of the research team will measure height to the nearest centimeter using a stadiometer (Harpenden pocket stadiometer Practical Metrology) and body weight to the nearest 0.1 kg (TANITA, Arlington Heights). BMI will be calculated and categorized according to standard cutoffs [26].

#### Dietary Assessment

A researcher (CF) who is also a registered nutritionist will use the malnutrition universal screening tool as recommended by the European Society for Clinical Nutrition and Metabolism to assess the risk of malnutrition [27].

#### Physical Function

Participants will be asked to complete the 5-times sit-to-stand physical function test. The 5-times sit-to-stand requires participants to rise from a chair 5 times as quickly as possible with arms folded across their chest and the researcher will record the time taken to complete the task. The researcher will then calculate lower limb muscle power using the validated equation developed by Kirk et al [28] and Alcazar et al [29]. Grip strength will be assessed on a Takei 5001 analog hand grip dynamometer (Takei Scientific Instruments Co, Ltd) 3 times on each hand with the best score used for analysis.

#### Quality of Life

The participants’ perceived state of health and quality of life will be assessed using the validated EQ-5D questionnaire in combination with the EQ-5D-5L [30]. The EQ-5D questionnaire comprises 5 questions assessing mobility, self-care, usual activities, pain or discomfort, and anxiety or depression to produce an overall score representing the participant’s health profile. The score will range from 1 (full health) to 0 (state of health equitable to death), with the option to have negative values representing a state of health considered to be worse than death [31]. The EQ-5D-5L is a visual scale ranging from 0 (worst health imaginable) to 100 (best health imaginable), where participants indicate how they perceive their current health status both on a number line and numerically [31].

#### Mood

Participants will complete the 4-item Geriatric depression scale as part of the baseline questionnaire, given that mood can affect motivation and may affect the use of KOKU-Nut.

#### Frailty

The researcher will assess frailty status based on the descriptions and pictographs included in the clinical frailty scale, which has been well validated and is frequently used in adults aged 65 years and older [32,33].

### Data Monitoring and Management

All digital and physical data will be stored securely at the University of Manchester and securely destroyed at the end of the data retention period as stated in the data management plan. Digital data will be stored on a backup drive on the university’s central server accessible by the research team. On enrollment to the study, all participants will be assigned a unique identification number with all subsequent data stored against this pseudonymized number. Identifiable information (such as name and contact details) will be stored separately and will only be linked to study-collected data through a recruitment log which will be password protected and file access will be limited to researchers working on the study. All printed documentation including consent forms and participants’ case files will be stored in a locked storage cabinet in a designated location at the University of Manchester. Interviews will be recorded on an encrypted Dictaphone. Audio recordings will be securely destroyed (digitally shredded) from the Dictaphone after being transcribed and validated by a member of the research team.

### Statistical Analysis

All quantitative data will be analyzed in STATA (version 15; StataCorp). The primary outcome will be calculated with regard to the indicators of feasibility to investigate engagement with the intervention, recruitment and retention rates, and acceptability of the intervention and study design. These will be summarized appropriately using descriptive statistics including percentages, mean with SDs, and ranges. Pre-post intervention changes in health measures will be analyzed in an exploratory fashion to gain preliminary insights into the number of valid versus missing data and to assess how outcomes are associated with group assignment and intervention engagement. Effect sizes will be determined using Cohen *d* to calculate sample sizes for a powered RCT.

Qualitative interview transcripts will be managed using NVivo software (version 12; QSR International Pty Ltd) and analyzed using an inductive approach with the 5 stages of framework analysis [34,35] to understand any barriers to the recruitment process, the suitability of the assessment measures, and the practicality of using the KOKU-Nut intervention. The first stage of framework analysis involves familiarization of the data from the transcripts and audio-recordings. The second stage involves classifying the data into codes and identifying a thematic framework from the key themes identified. The third stage involves systematically indexing the data using the framework identified. The fourth stage involves charting and synthesizing the data to categorize and capture key concepts and themes. The final stage involves the mapping and interpretation of the data [34]. All stages of the analysis process will be discussed and reviewed with at least 2 researchers (ES and SB) to ensure rigor [36].

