Secondary outcomes will consider the usability and safety of the intervention and the practicality of collecting and assessing the effectiveness of KOKU-Nut compared to an information booklet about healthy living. The perceived usability of KOKU-Nut will be assessed using the validated 10-item system usability scale. Responses are measured on a 5-point Likert scale ranging from 1 (strongly disagree) to 5 (strongly agree). A score >68 is considered above-average usability and >80 is considered high usability such that participants are likely to recommend the product to peers. The safety of the intervention will be based on the number of adverse events that occurred as a result of participation in the study. We will consider the practicality of collecting effectiveness data by documenting the amount and rationale for any missing data. Changes in means and SDs will be compared to consider the preliminary effectiveness of the intervention and to calculate sample sizes for a future trial. The study will be assessed against progression criteria based on Shanyinde et al [21] to determine progression to a powered RCT. Figure 1 shows the schedule of the intervention and assessment according to the SPIRIT statement.

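### The exploratory group comparison is based on pre-post change and feeds a Cohen d into the next trial's sample size, with no mention of baseline adjustment or of the SD that standardises d

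*Protocol article*

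**What the plan says.** Two sections of the protocol article describe how the health measures will be compared. Statistical Analysis states that "Pre-post intervention changes in health measures will be analyzed in an exploratory fashion", one purpose being "to assess how outcomes are associated with group assignment and intervention engagement". Outcomes states that "Changes in means and SDs will be compared to consider the preliminary effectiveness of the intervention", and gives the sample size of a future trial as a further use.

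Statistical Analysis then says: "Effect sizes will be determined using Cohen" *d*, "to calculate sample sizes for a powered RCT". The standardising SD (baseline, follow-up or change) is not named.

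The data for an adjusted analysis will exist. Under Data Collection Methods (Overview), at the end of the 12 weeks "all baseline measures will be repeated". Under Allocation, participants are "stratified by age group (65-75 years and 76 years and older), gender, and prior experience of using a tablet or iPad". No section names a model for the group comparison, and none rules covariates in or out.

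**The concern.** Change from baseline is the only basis for a group comparison that the protocol names. Subtracting the baseline treats the regression of follow-up on baseline as having slope 1. Where the correlation is below 1 the true slope is smaller (for equal SDs), so the subtraction adds noise. In a trial this small, that imprecision matters for the one effectiveness quantity it is meant to pass on: preliminary effect sizes are a stated secondary aim, and *d* is to size the powered trial.

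The second difficulty is the scale of *d*. The same raw difference gives different values of *d* depending on the SD used as divisor, and the ratio between them depends on a correlation that the protocol does not say it will report. Someone planning the next trial from the published *d* alone could not tell which design it fits.

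**Working it through.** **Inputs from the protocol.** 18 per arm, 1:1, with 20% dropout (Sample Size). Applying 20% dropout to 36 gives 36 × 0.8 = 28.8, so about 28 completers, n = 14 per arm. The protocol gives no precision or effect-size figure for these measures, so there is none to reproduce.

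**Assumptions, not in the protocol.** The baseline-to-follow-up correlation r, shown as a range; equal SDs at baseline and follow-up, set to 1; for the sample-size illustration, a raw *d* of 0.40, two-sided alpha 0.05 and 80% power.

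**Step 1: precision.** Per person, the variance of a change is 2(1 − r), and the residual variance after baseline adjustment is 1 − r². In large samples the SE ratio, change over adjusted, is √(2/(1 + r)): 1.24, 1.15, 1.08 and 1.03 at r = 0.3, 0.5, 0.7 and 0.9. For N = 28, allowing for degrees of freedom and chance baseline imbalance, the 95% half-widths are:

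- change: t(0.975; 26) × √(2(1 − r)) × √(2/14)
- adjusted: t(0.975; 25) × √(1 − r²) × √(2/14) × √(25/24)

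| r | Change | Baseline-adjusted | Ratio |
|---|---|---|---|
| 0.3 | 0.919 | 0.758 | 1.21 |
| 0.5 | 0.777 | 0.688 | 1.13 |
| 0.7 | 0.602 | 0.567 | 1.06 |
| 0.9 | 0.347 | 0.346 | 1.00 |

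Half-widths are in outcome SDs. If all 36 completed, the ratios would be 1.22, 1.14, 1.07 and 1.01. A simulation at r = 0.5, 0.7 and 0.9 agreed closely (N = 28, r = 0.5: 0.771 against 0.682).

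**Step 2: adding the three stratification factors.** If they carry no prognostic information beyond baseline, the N = 28 half-widths depend on how well stratification balances them:

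| r | Change | Adjusted, factors balanced | Adjusted, factors not balanced |
|---|---|---|---|
| 0.5 | 0.777 | 0.693 | 0.741 |
| 0.7 | 0.602 | 0.571 | 0.611 |
| 0.9 | 0.347 | 0.349 | 0.373 |

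Without good balance the gain has gone by r = 0.7.

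**Step 3: scale of *d*.** *d* on the change SD equals *d* on the outcome SD divided by √(2(1 − r)). Required n varies as 1/*d*², so reading a change-scale *d* as an outcome-scale *d* multiplies n by 2(1 − r). On the outcome scale, *d* = 0.40 needs 99 per arm.

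| r | *d* on change SD | n per arm from that *d* | Against 99 per arm |
|---|---|---|---|
| 0.3 | 0.34 | 138 | 1.4 times too large |
| 0.5 | 0.40 | 99 | correct |
| 0.7 | 0.52 | 59 | too small by 1.7 |
| 0.8 | 0.63 | 40 | too small by 2.5 |

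These errors arise only if the next trial compares follow-up values. If it compares changes, the change-scale *d* is on the right scale.

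**The case against.** The strongest reply is that the protocol fixes very little here. It names no model, and a change outcome can itself be fitted with baseline as a covariate, in which case the arm estimate equals that from an adjusted analysis of the 12-week value. Model form and covariates are commonly left to an analysis plan, which is not shown. The analysis is labelled exploratory, the trial is not designed to detect differences, and no confidence interval is promised for these measures.

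Much of this stands, and it rules out three stronger readings that a reader might infer:

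- That the protocol commits to an unadjusted analysis that ignores the stratification factors. It says neither; this would be an inference from silence.
- That *d* will be on the change-SD scale. The divisor is simply not stated.
- That the next trial will be undersized. The error can go in either direction or vanish, depending on r, and it needs two events that the protocol does not describe: division by the change SD, and sizing for a comparison of follow-up values.

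Nor is change-score analysis biased under randomisation; the loss is in precision. What the objection does not remove is that change is named twice as the basis of comparison, that the resulting *d* has a declared use, and that the better estimate needs no new data.

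**Conclusion.** The point holds as a minor improvement to an exploratory secondary analysis. With about 28 completers, relying on change without adjustment would cost about 21%, 13% and 6% in interval width at r = 0.3, 0.5 and 0.7, and almost nothing at r = 0.9. An undefined *d* could move the next trial's n from 1.4 times too large to 2.5 times too small over r = 0.3 to 0.8, but only under the two conditions in the working.

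These sizes rest on the assumed r and equal SDs. The interval is used here as a yardstick of precision, not as an output the protocol promises. The statement that change scores are unbiased also assumes that allocation does not affect the baseline reading. The Recruitment section places randomisation before baseline measurement, and Allocation says participants and researchers are unblinded, so this is worth keeping in mind. Any such shift would carry over in full to a change score and in proportion r to an adjusted estimate. The descriptive feasibility outcomes are not affected.

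**What to change.** In Statistical Analysis, and to match in Outcomes, state that for each continuous health measure the between-group difference at 12 weeks will be estimated from a linear model with arm and baseline value. Report it in raw units with a 95% CI, together with the outcome SD, the residual SD and the baseline-to-follow-up correlation. The next trial can then be sized for whichever analysis it adopts. If a Cohen *d* is shown, standardise it by the pooled baseline SD and say so.

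The three stratification factors may be added as covariates. This costs three degrees of freedom and may forfeit the precision gain if they are not prognostic, so baseline adjustment is the essential part.

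The cost is a change of analysis wording. No new data, visits or participants are needed, and the baseline term uses one degree of freedom.
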